### Randomisation, concealment and blinding

Patients are randomly assigned in a 2:1 fashion to intravenous methylprednisolone or placebo in blocks of six, following stratification by either anti-centromere or anti-topoisomerase auto-antibodies, sex and age. Patients will be randomly assigned by using Castor, an online data collection tool for medical research. Randomisation will result in the allocation of a unique number to each patient. Physical examinations for efficacy outcomes are performed by a researcher who is blind to the occurrence of both mild and serious adverse events. The physicians who accompany the intervention and perform assessments for vital status and adverse events do not assess the efficacy outcomes. To maintain the overall quality and legitimacy of the clinical trial, the randomisation code can be broken only when knowledge of the actual treatment is absolutely necessary for further management of the patient or at the request of the safety monitoring committee.

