## Methods/design

This 12-week, double-blind, randomised, placebo-controlled trial is under way (inclusion began on January 1, 2017, and is open until July 1, 2018) at the Department of Rheumatology of Radboud University Medical Centre in Nijmegen, The Netherlands.

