### Study design rationale

In order to investigate the effect of high-dose methylprednisolone in very early SSc, we have designed a randomised, placebo-controlled, double-blind, mono-centre superiority trial with a primary endpoint of changes in nailfold capillary density after 12 weeks. Randomisation will be performed in blocks of six after the stratification of anti-centromere/anti-topoisomerase auto-antibodies, sex and age and there will be a 2:1 patient allocation to groups receiving intravenous methylprednisolone or placebo.

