### Trial status

Open for inclusion.

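### A single disclosed block length of six, in a single-centre trial with a saline placebo, would let staff who recognise steroid effects deduce some later allocations within a stratum

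*Protocol article*

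**What the plan says.** The block length is given twice, and the two places agree. Under Study design rationale: "Randomisation will be performed in blocks of six after the stratification of anti-centromere/anti-topoisomerase auto-antibodies, sex and age". Under Randomisation, concealment and blinding: "Patients are randomly assigned in a 2:1 fashion to intravenous methylprednisolone or placebo in blocks of six". The latter section names the same three stratification factors. No second block length is mentioned. The trial is a "mono-centre superiority trial".

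Allocation runs through an online system, and the placebo is a saline solution identical in appearance (Investigational product/treatment). The efficacy examiner is kept blind to adverse events, and "The physicians who accompany the intervention and perform assessments for vital status and adverse events do not assess the efficacy outcomes".

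On timing, Methods/design states that "inclusion began on January 1, 2017, and is open until July 1, 2018". Trial status reads "Open for inclusion", in an article dated 22 August 2018.

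**The concern.** With one known length, a block's composition is known in advance. Once both placebo places in a stratum's block have been recognised, every remaining patient in that block will receive methylprednisolone. Once four active places have been recognised, the rest will receive placebo.

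The protocol itself treats adverse events as potentially unblinding, since it shields the efficacy examiner from them. The physicians at the infusions do see them. Nothing in the article withholds the block length from those physicians or keeps them out of recruitment. Keeping the efficacy examiner separate protects the measurement of capillary density. It does not protect the decision on who is entered next, or when. With only 10 placebo patients, a few steered entries could matter, and adjustment for measured covariates cannot fully remove selection on unmeasured prognosis.

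**Working it through.** **Inputs from the article.** Block of six at 2:1 (4 active, 2 placebo); stratification by antibody, sex and age; 30 patients (20 + 10); SD 0.9; target difference nearly 1.0.

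**Assumptions.** Two or three age groups (no cut-offs are given), hence 8 or 12 strata; the stratum proportions below; every earlier allocation in the stratum recognised correctly. The last makes the results upper bounds on what is certain.

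**1. The plan's own figure.** The detectable difference with 20 v 10 is 0.9 × (1.960 + 0.842) × √(1/20 + 1/10) = 0.98. This agrees with the stated difference of nearly 1.0. The sample size is not in dispute.

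**2. One completed block.** There are C(6,2) = 15 equally likely orders. A place is determined when one arm's places are already used up.

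| Place | Orders in which it is determined | Share |
|---|---|---|
| 1 | 0 | 0% |
| 2 | 0 | 0% |
| 3 | 1 (both placebos in the first 2) | 6.7% |
| 4 | C(3,2) = 3 | 20% |
| 5 | C(4,2) + 1 = 7 (the 1 is four actives first) | 46.7% |
| 6 | 15 | 100% |

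Total: 26 of 15 × 6 = 90 places, or 28.9% (1.73 per block). Of these, 1 + 3 + 6 + 10 = 20 are active (77%) and 6 are placebo.

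**3. Thirty patients over strata.** Patients were split at random over the strata and the shares above were applied to the places reached.

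| Strata | Determined, of 30 | Share |
|---|---|---|
| None (one list) | 8.7 | 28.9% |
| 8 equal | 3.8 | 12.5% |
| 12 equal | 1.9 | 6.4% |
| 8 uneven (85% one sex, 70% one antibody, two equal age groups) | 5.1 | 17.1% |
| 8 uneven (85%, 80%, two equal age groups) | 5.3 | 17.6% |
| 8 uneven (90%, 80%, two equal age groups) | 5.6 | 18.6% |
| 12 uneven (85%, 70%, three equal age groups) | 4.1 | 13.7% |

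The stratified range is about 6% to 19%.

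**4. Varying lengths.** The strata are those of the 17.6% row. The observer knows the set of lengths but not their order. Determined places fall from 17.6% to about 6% with lengths 3 and 6, and to about 2% with lengths 3, 6 and 9. The rate at which that observer's best guess is right hardly moves: about 71% with fixed sixes and about 71% with 3, 6 and 9. Always guessing active is right 67% of the time.

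**5. Imperfect recognition.** With fixed sixes and the same strata, an allocation that appears determined is in fact as deduced 83% of the time if each earlier one is recognised with 90% accuracy, 74% at 80% accuracy and 69% at 70% accuracy. The article gives no recognition rate.

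**The case against.** Permuted blocks of one length within strata are a recognised method, and the two statements of it agree. Allocation is online, the infusions look alike, and code-breaking is restricted. To exploit the block, someone must see the reactions, track strata and order, and influence entry. The article does not say who enrols patients, and a condensed article may leave that to the full protocol. Recognition will be imperfect, and at 70% to 80% accuracy little is gained over always guessing active. All of this stands, and it limits the size of the point. It does not remove the point: the article itself fixes and discloses the length, and none of the safeguards it lists conceals what follows from a known length.

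Three stronger readings should be resisted.

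- *Later allocations in general can be worked out with certainty.* Only a minority can, and only with error-free recognition within each stratum.
- *The length was published while patients were still being entered.* The article does not establish this. One section ends inclusion on 1 July 2018, before the publication date, and another says the trial is open.
- *The result would be biased by a known amount.* If the 5.3 determined places (4.2 active, 1.1 placebo) went to patients 0.5 SD (0.45) better on active and 0.45 worse on placebo, the shift would be 4.2/20 × 0.45 + 1.1/10 × 0.45 = 0.14, against a target of nearly 1.0. That needs perfect recognition, deliberate selection at every determined place, and suitable candidates waiting in the right stratum. The 0.5 SD has no source in the article, and the planned analysis of covariance could absorb part of such a shift if it adjusts for baseline density. It is an illustrative worst case, not an estimate.

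**Conclusion.** The point holds as a minor, inexpensive improvement to allocation concealment. The fixed, disclosed block of six makes some late-in-block allocations deducible by staff who recognise earlier ones: 28.9% of places in a completed block, and roughly 6% to 19% of the 30 patients, or about 2 to 6 people. Both figures assume error-free recognition, and the second also depends on the assumed strata. The article gives no evidence that anyone has used or would use this. The bias is therefore possible but unquantified.

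**What to change.** For all blocks not yet opened, replace the fixed length with randomly varying lengths in multiples of three (for example 3, 6 and 9) within strata, keeping the 2:1 ratio and the stratification factors. The protocol should say only that lengths vary and are withheld from site staff. The lengths and their set belong in a restricted randomisation file. The gain depends on this: if the set leaks, certain allocations still fall, but overall guessability does not.

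The cost is a change to the randomisation settings and one sentence, with no added patients, visits or staff. Patients already randomised remain under fixed blocks, and the final split within a stratum may differ by a patient or so.

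The inclusion period in Methods/design and the statement under Trial status should be reconciled. If inclusion has closed, the change can no longer help, and the fixed block length should be reported as a limitation.

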### Statistical analysis

The data will be analysed primarily according to the intention-to-treat principle. Missing values due to participant drop-out are treated according to the last observation carried forward. A *P* value of 0.05 will be used to denote statistical significance for between-group differences in the primary outcome.

Between-group differences in the change in efficacy outcome variables between the baseline and week 12 will be analysed by using an analysis of covariance or logistical regression. Similarly, the ongoing changes to the continuous outcomes will be analysed between the baseline and weeks 4, 8 and 12 by using a repeated-measures analysis of variance.

Serious and minor adverse events will be tabulated by group, and depending on the occurrence, a time-to-event analysis may be used to analyse between-group differences in serious adverse events. The use of any immunosuppressive therapy between week 12 and the 1-year follow-up will be described for each of the two groups.

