### Outcome measures

#### Primary outcome

In this study, the primary endpoint will be the change in capillary density between the baseline and after 12 weeks of treatment.

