#### Secondary outcomes

The secondary outcomes (all compared between the baseline and week 12 or between the baseline and 1 year) of this study are (a change in):selected biomarkers: the interferon signature in peripheral blood cells, CXCL4, interleukin-1 beta (IL-1β), IL-6, tumor necrosis factor-alpha (TNF-α), ET-1, intercellular adhesion molecule 1 (ICAM-1) and vascular endothelial growth factor (VEGF) [3, 23–27];nailfold capillary changes other than capillary density and the presence of giant capillariesan mRSS; the presence of puffy fingers; the presence of synovitis; the presence of tendon friction rubs; fulfilling EULAR/ACR classification criteria for SSc [28];pulmonary function tests; the presence of interstitial lung disease; a suspicion of pulmonary hypertension; andphysical function, general health and utilities as measured by the Scleroderma Health Assessment Questionnaire (SHAQ), 36-Item Short Form Health Survey (SF-36), EuroQOL five dimensions questionnaire (EQ5D) and Gastrointestinal Tract Questionnaire (GIT).

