### Assessments

Regular visits are planned at the baseline and after months 1, 2, 3, 6, 9 and 12. See Fig. 1—according to the Additional file 1: SPIRIT (Standard Protocol Items: Recommendations for Interventional Trials) checklist—for an overview of all visits and assessments.

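### Last observation carried forward is the only rule for drop-out; it can bias the week-12 capillary-density difference, most plausibly towards no effect, and a missing-at-random analysis should replace it

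*Protocol article*

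**What the plan says.** Under Primary outcome, "the primary endpoint will be the change in capillary density between the baseline and after 12 weeks of treatment". Under Statistical analysis, "The data will be analysed primarily according to the intention-to-treat principle", and the next sentence gives the missing-data rule: "Missing values due to participant drop-out are treated according to the last observation carried forward". It is not restricted to particular outcomes, and no justification or alternative is given.

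The same section compares change "between the baseline and week 12 will be analysed by using an analysis of covariance or logistical regression", and adds that continuous outcomes are "analysed between the baseline and weeks 4, 8 and 12 by using a repeated-measures analysis of variance". Under Assessments, "Regular visits are planned at the baseline and after months 1, 2, 3, 6, 9 and 12". The table of procedures (Fig. 1) is not reproduced in the text at hand, so it cannot be confirmed that capillaroscopy is done at weeks 4 and 8.

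**The concern.** This is a stated method, not a detail left for the statistical analysis plan. It fixes how the primary result is computed for anyone who leaves early.

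The rule assumes that density freezes at the last visit. The trial's reasoning points the other way: the Sample size section cites a 12-week gain of 1.5 after stem cell transplantation, and the Study outcome rationale lists capillary loss among the typical changes in this disease. A patient lost before any follow-up capillaroscopy is scored as exactly zero change. The filled-in value then enters the ANCOVA as if it had been measured, so uncertainty is understated. A classical repeated-measures ANOVA needs complete rows and so relies on the same filled-in values.

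The design has little reserve. It has 10 placebo patients, about 80% power for a difference near 1.0, and no stated drop-out allowance.

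**Working it through.** **1. The plan's own figure.** Inputs from Sample size: alpha 0.05 (taken as two-sided), power 0.80, SD 0.9, 20 active and 10 placebo. Detectable difference = (1.960 + 0.842) × 0.9 × √(1/10 + 1/20) = 2.802 × 0.3486 = 0.977. This reproduces the stated value of nearly 1.0. By noncentral t, power at 1.0 is 0.79.

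**2. Expected value under LOCF.** Assumptions, not from the document: change is linear over 12 weeks, and drop-out is spread evenly after baseline, week 4 and week 8. A drop-out is then credited on average with (0 + 1/3 + 2/3)/3 = 1/3 of the true change. With mean changes Δ_A and Δ_P and drop-out proportions d_A and d_P,

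bias = −(2/3)(Δ_A·d_A − Δ_P·d_P).

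If density is measured only at baseline and week 12, the factor 2/3 becomes 1.

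| Δ_A, Δ_P | Drop-out active/placebo | Truth | LOCF estimate | Baseline carried forward |
|---|---|---|---|---|
| +1.0, 0 | 10%/10% | 1.0 | 0.93 | 0.90 |
| +1.0, 0 | 20%/20% | 1.0 | 0.87 | 0.80 |
| +1.0, 0 | 30%/10% | 1.0 | 0.80 | 0.70 |
| +1.5, 0 (the cited benchmark) | 20%/20% | 1.5 | 1.30 | 1.20 |
| 0, 0 | any | 0 | 0 | 0 |
| −1.0, −1.0 | 20%/20% | 0 | 0 | 0 |
| −1.0, −1.0 | 25%/5% | 0 | +0.13 | +0.20 |
| −1.0, −1.0 | 5%/30% | 0 | −0.17 | −0.25 |

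**3. Outcome-related drop-out.** Simulation, 4,000 runs, 20 and 10 patients. Assumed: SD 0.9, visit correlations 0.6 to 0.7, linear change, and drop-out after week 4 or 8 more likely after a poorer value.

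- Active +1.0, placebo flat: LOCF averages 0.96 (10%/10%), 0.92 (20%/20%) and 0.85 (30%/10%). A likelihood estimate under missing at random averages 1.00 in each.
- Both arms −1.0, no drug effect: LOCF averages +0.10 (30%/10%) and −0.11 (10%/30%). The likelihood estimate averages about 0.00.
- Both arms flat, no drug effect: LOCF averages −0.03 (30%/10%) and +0.05 (10%/30%), with rejection rates of 5.4% and 5.7%.
- Across all scenarios, the SD of the estimate is about 0.33 to 0.37 with LOCF and 0.37 to 0.43 with the likelihood method.

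**4. Power.** With 20% lost per arm, 16 and 8 patients remain. The standard error is 0.9 × √(1/16 + 1/8) = 0.39, and noncentral t power at 1.0 is 0.69. Simulated with random slopes and visit noise of 0.4, LOCF rejects in about 70% of runs and observed-case analysis in about 68%. If only baseline can be carried forward, LOCF rejects in about 64%.

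**The case against.** Several points on the other side stand.

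- **Power.** A reader might blame LOCF for the fall from 0.79 to about 0.70. That loss comes from the missing patients, since observed-case analysis gives 0.68 to 0.69 at the same drop-out. In the attenuation case LOCF's total error is no worse either: √(0.133² + 0.33²) = 0.36, against an observed-case standard error of 0.39.
- **False positives.** A reader might infer that LOCF is likely to manufacture a benefit. In the both-arms-decline case with 25%/5% drop-out, simulated type I error is 6.7% to 9.2%. But that needs both arms to lose 1.0 within 12 weeks. The only 12-week figures in the document are no change in controls and a gain with transplantation. They come from progressive disease, so they are not proof for this population, but nothing in the document supports a 12-week loss of that size.
- **Informative drop-out.** The Escape treatment section might be read as making drop-out follow worsening. It stops study treatment; it does not say that the patient leaves follow-up.
- **One-year outcomes.** Secondary outcomes are "all compared between the baseline and week 12 or between the baseline and 1 year", which might suggest a week-12 value carried for nine months. Visits at months 6 and 9 make that a special case, and the analysis section names no one-year efficacy test.
- **An over-heavy remedy.** Over three follow-up visits, visit means (3), treatment by visit (3), baseline by visit (3) and an unstructured covariance (6) make 15 parameters from 30 patients.

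The document also calls the trial a pilot, and an unseen analysis plan may hold sensitivity analyses. That lowers the severity, but it does not make the stated primary rule sound.

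**Conclusion.** The point holds in conditional form: LOCF can bias the primary comparison. It does no harm with no drop-out, or when drop-out is equal and there is no drug effect. In the scenario closest to the document, it shrinks a true difference of 1.0 by about 0.13 (0.20 if only baseline can be carried forward) at an assumed 20% drop-out per arm. With no drug effect, a shift of +0.13 to +0.20 or −0.17 to −0.25 appears only if both arms decline by 1.0 and drop-out is clearly unequal; with flat arms the simulated shift was 0.05 or less. These sizes rest on assumed drop-out rates and linear change. Treating imputed values as observed is a defect at any size. Should be fixed; not fatal.

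**What to change.** Replace LOCF as the primary rule with an analysis valid under missing at random, before unblinding.

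- **If capillaroscopy is done at weeks 4, 8 and 12:** fit a likelihood-based mixed model to the observed visits, with treatment, visit, their interaction and baseline density as covariate. Use a covariance structure simple enough for 30 patients, or an unstructured one with a pre-stated fallback if it fails to converge, and a small-sample degrees-of-freedom correction such as Kenward-Roger. The week-12 contrast is primary. This model also replaces the repeated-measures ANOVA.
- **If density is measured only at baseline and week 12:** use baseline-adjusted ANCOVA on observed values, or multiple imputation to keep all randomised patients in the analysis.
- **Sensitivity:** add one delta-adjusted (tipping-point) analysis. LOCF may stay as a further sensitivity analysis.

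The cost is analysis wording only; the sample size and visits do not change. The downside is a wider confidence interval: in simulation the SD of the estimate was about 0.37 to 0.43 against 0.33 to 0.37 with LOCF. No gain in power should be promised.

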### Sample size

The effect of high-dose methylprednisolone on nailfold capillary changes and other outcomes in early SSc is unknown; therefore, the optimal size of a pilot trial is unknown. If the sample is too small, the estimate of the effect will be too uncertain. If the sample is too large, it may be judged as unnecessarily exposing participants to risks and burdens and therefore as being unethical. Furthermore, setting the sample size too high may lead to a preventable failure to reach the recruitment target. To minimise the risk for participants and maximise the information gained, we judged that the inclusion of 30 patients (20 in the treatment arm and 10 in the placebo arm) would be appropriate for this pilot study. When adopting the usual alpha of 0.05, power of 0.80, standard deviation of 0.9 and randomisation scheme of 2:1, a between-group difference of nearly 1.0 in the capillary density score thus would represent a statistically significant difference, using the standard sample size formula. In previous ASCT treatments for SSc, the change in capillary density over the first 12 weeks was 1.5 in the intervention group, and there was no change in the control group [20]. Patients are randomly assigned at a 2:1 ratio to maximise the information about the experimental intervention, which can be justified as the risks of the intervention are known and relatively low.

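### Logistic regression is the only method named for binary outcomes at 20 v 10 patients; for uncommon events an arm will often be empty, leaving the ordinary odds ratio and its Wald interval unusable

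*Protocol article*

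**What the plan says.** The Statistical analysis section of the protocol article states that between-group differences in the change from baseline to week 12 "will be analysed by using an analysis of covariance or logistical regression". Analysis of covariance serves the continuous outcomes, which leaves logistic regression for the binary ones. The section names no estimation variant, no type of test and no alternative for sparse tables.

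The Sample size section sets the trial at "30 patients (20 in the treatment arm and 10 in the placebo arm").

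The Secondary outcomes section lists six binary outcomes in two groups: "the presence of puffy fingers; the presence of synovitis; the presence of tendon friction rubs; fulfilling EULAR/ACR classification criteria for SSc", and "the presence of interstitial lung disease; a suspicion of pulmonary hypertension". Signs and symptoms of progression are part of what the Secondary objectives section calls the key secondary objective.

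No event rates are given. Entry conditions point to low counts for several outcomes. The Exclusion criteria remove clinically significant organ involvement, including pulmonary hypertension. The Inclusion criteria require a skin score of 0. The Discussion says that patients who already meet the 2013 classification criteria are not included.

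**The concern.** Maximum-likelihood logistic regression needs both events and non-events in each arm. When one arm has no events, or only events, the treatment log odds ratio runs off to plus or minus infinity, its standard error explodes and the Wald P value goes to about 1 however large the difference in counts. With 10 placebo patients and uncommon outcomes this is an ordinary result, not a remote one.

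At stake are the usable effect estimates for the clinical progression outcomes. For a trial that calls itself a pilot, the estimate and its interval matter more than the P value. The breakdown can also hide a real difference in either direction, benefit or harm. If the model fails after unblinding, a substitute method would have to be chosen with the data in view.

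**Working it through.** **Inputs.** From the article: 20 active and 10 placebo patients; logistic regression for binary outcomes. Assumed: event rates of 5% to 40%, because none are stated; no drop-out; a model with treatment only.

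**The plan's own figure.** The Sample size section claims power for "a between-group difference of nearly 1.0 in the capillary density score" with SD 0.9. The normal formula, two-sided, gives 0.9 × √(1/10 + 1/20) × (1.960 + 0.842) = 0.977, so the figure reproduces. It concerns the continuous primary outcome and says nothing about the binary ones.

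**Step 1: how often is an arm empty or full?** With true rates p_A (active) and p_P (placebo):

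P = 1 − [1 − (1−p_A)^20 − p_A^20] × [1 − (1−p_P)^10 − p_P^10]

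At 5% in both arms, 0.95^20 = 0.358 and 0.95^10 = 0.599, so P = 1 − 0.642 × 0.401 = 0.743.

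| Active / placebo rate | P(empty or full arm) |
|---|---|
| 5% / 5% | 74% |
| 10% / 10% | 43% |
| 20% / 20% | 12% |
| 25% / 25% | 6% |
| 5% / 20% | 43% |
| 5% / 30% | 38% |
| 5% / 40% | 36% |

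The 74% includes 0.358 × 0.599 = 21.5% of trials with no event in either arm, where no method can show a difference.

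**Step 2: what does the model return?** Fits with treatment only:

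| Active v placebo | Log OR when iteration stops | SE | Wald P | Likelihood-ratio P | Fisher P |
|---|---|---|---|---|---|
| 0/20 v 2/10 | −22.2 | 17,770 | 0.999 | 0.030 | 0.103 |
| 0/20 v 3/10 | −22.7 | 17,770 | 0.999 | 0.007 | 0.030 |
| 0/20 v 4/10 | −23.2 | 17,770 | 0.999 | 0.001 | 0.008 |
| 10/20 v 0/10 | +22.6 | 15,240 | 0.999 | 0.001 | 0.011 |

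The active-to-placebo odds ratio is 0 when the active arm is empty, infinite when the placebo arm is empty, and undefined when both are.

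**Step 3: how often does this hide something detectable?** With 0/20 on active, Fisher's test falls below 0.05 only from 3/10 placebo events upward. The main term is therefore P(0 of 20 active) × P(at least 3 of 10 placebo):

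- 5% v 20%: 0.3585 × 0.3222 = 0.116
- 5% v 30%: 0.3585 × 0.6172 = 0.221
- 5% v 40%: 0.3585 × 0.8327 = 0.299

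At equal rates, counting empty or full cells in either arm, it is 0.4% (5%), 0.9% (10%) and 0.7% (20%).

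**Step 4: cross-check by exact enumeration of power.** At 5% v 30%: Wald 16.4%, Fisher 38.5%. At 5% v 40%: Wald 31.5%, Fisher 61.3%, Firth 62.5%, likelihood ratio 66.8%. The Fisher-minus-Wald gaps, 22.1 and 29.8 points, match step 3.

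**Step 5: false-positive rates at a nominal 5%.** At 10% in both arms: likelihood ratio 5.1%, Fisher 1.3%, Firth 1.4%. At 20%: 7.0%, 2.2% and 3.4%.

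**Step 6: the alternative in an empty table.** For 0/20 v 4/10, Firth gives an odds ratio of (0.5/20.5)/(4.5/6.5) = 0.035 with penalised likelihood-ratio P = 0.004. The risk difference is 0 − 0.40 = −40 percentage points.

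**The case against.** The strongest reply is that the article never says ordinary, maximum-likelihood or Wald. Firth regression is itself a form of logistic regression, so it fits the stated text, and a statistical analysis plan that is not shown may specify it. A likelihood-ratio test from the same model does not collapse. This stands in part: a reader should not infer that the plan commits to Wald P values, because it does not. But the unqualified term ordinarily means the maximum-likelihood fit, and in an empty table that fit has no finite odds ratio whichever test accompanies it.

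A second reply is that the chance of an empty arm overstates the damage. This stands. One might read the 74% as the share of trials reaching a wrong conclusion. The documents do not support that: at equal rates there is no difference to miss, and a detectable difference is hidden in under 1% of trials. The larger losses need placebo rates of 20% to 40% by week 12, and an outcome at 30% or 40% is no longer rare.

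Third, the outcomes differ. Puffy fingers appear in the entry criteria and may be common; synovitis and tendon friction rubs are not excluded at entry. This also stands, and the point should be confined to outcomes that prove uncommon.

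Finally, the failure is conspicuous and the raw counts remain reportable. That limits the risk of a misleading report, but does not provide an effect estimate or a method chosen in advance.

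**Conclusion.** The point holds, with modest reach. The only method named for binary outcomes, in its usual form, will often give no usable odds ratio or Wald interval for uncommon outcomes at 20 v 10: in 74% to 43% of trials at 5% to 10% in both arms, 12% at 20%, and 6% or less from about 25%. The loss of a difference that Fisher's test would detect is smaller: about 12% of trials at 5% active v 20% placebo and 22% to 30% at 5% v 30% to 40%, if Wald P values are used.

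All event rates are assumptions. That several outcomes are uncommon is inferred from the entry criteria and the Discussion; the likeliest are interstitial lung disease, suspected pulmonary hypertension, tendon friction rubs and newly fulfilled classification criteria.

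A reader might infer that the trial's main result is threatened. It is not: capillary density is continuous, and the article ties its 0.05 threshold to the primary outcome alone. The change is worth making because it is cheap and affects outcomes under the key secondary objective.

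**What to change.** In the analysis plan, before unblinding, state that each binary outcome will be reported as counts by arm and as a risk difference with an exact or score-based 95% confidence interval, with an exact test (Fisher's or an unconditional exact test). Where covariates are wanted, name Firth penalised logistic regression with profile-likelihood intervals. If an analysis plan already says this, only the article's wording needs to be aligned with it.

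The cost is a sentence or two, and standard software does the work. The downside is that exact tests are somewhat conservative (Fisher's false-positive rate is 1.3% to 2.2% at event rates of 10% to 20%), so the interval should carry the interpretation.

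### The analysis of weeks 4, 8 and 12 is named as an analysis of variance of change, which does not adjust for baseline; this costs precision and consistency in a supporting analysis

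*Protocol article*

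**What the plan says.** The Statistical analysis section of the protocol article gives two methods in consecutive sentences. Between-group differences in change "between the baseline and week 12 will be analysed by using an analysis of covariance or logistical regression". The next sentence names an analysis of variance for the visits up to week 12: "the ongoing changes to the continuous outcomes will be analysed between the baseline and weeks 4, 8 and 12 by using a repeated-measures analysis of" …

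No covariates are listed for either analysis. That the analysis of covariance adjusts for baseline is the natural reading of its name, but it is not stated. The baseline value is available: "Regular visits are planned at the baseline and after months 1, 2, 3, 6, 9 and 12" (Assessments).

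Under Primary outcome, "the primary endpoint will be the change in capillary density between the baseline and after 12 weeks of treatment", so the primary comparison belongs to the first of the two sentences. The Sample size section judges that "the inclusion of 30 patients (20 in the treatment arm and 10 in the placebo arm) would be appropriate" for a pilot study.

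**The concern.** The two sentences cover overlapping outcomes but name methods that treat baseline differently. A repeated-measures analysis of variance can be run in two ways here:

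- **Changes at the three visits as responses.** The whole baseline measurement error enters every change score.
- **Baseline as a fourth repeated level.** The treatment question moves to the group-by-time interaction on 3 degrees of freedom. Its contrasts against baseline are again differences in unadjusted change.

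Neither way uses baseline as a covariate. With 20 v 10 patients, chance baseline differences between the arms can be sizeable, and within a single trial an unadjusted change carries part of such a difference into the estimate. The only described analysis that uses all the on-treatment visits could therefore be less precise than the data allow. It could also show a week-12 difference that departs from the analysis of covariance of the same measurements.

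**Working it through.** **Inputs.** From the Sample size section: 20 v 10 patients, SD 0.9, alpha 0.05, power 0.80, detectable difference nearly 1.0. Assumed, because the article does not give them: correlation rho between any two visits (0.3 to 0.9), equal variances and compound symmetry, and 0.9 as the SD of a change from baseline.

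**The plan's own figure.** Two-sided normal formula: (1.960 + 0.842) × 0.9 × √(1/20 + 1/10) = 0.977. This reproduces the stated difference of nearly 1.0.

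**Variance of the three-visit mean**, in units of the single-visit variance σ²:

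- Mean change, unadjusted: (1 + 2rho)/3 + 1 − 2rho
- Adjusted for baseline: (1 + 2rho)/3 − rho²
- The ratio adjusted/unadjusted simplifies to (1 + 3rho)/4.

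At rho 0.5 the two variances are 0.667 and 0.417, ratio 0.625.

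**Power for a linear build-up** (0.33, 0.67, 1.0 at weeks 4, 8, 12; mean 0.667). With 0.9 as the SD of change, σ² = 0.81/[2(1 − rho)]. The unadjusted standard error is then √(0.81 × 2/3 × 0.15) = 0.285 at every rho, and the adjusted one is 0.285 × √ratio. Noncentral t, 28 df unadjusted and 27 df adjusted:

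| rho | variance ratio | unadjusted | adjusted |
|---|---|---|---|
| 0.3 | 0.475 | 0.619 | 0.906 |
| 0.5 | 0.625 | 0.619 | 0.815 |
| 0.7 | 0.775 | 0.619 | 0.727 |
| 0.9 | 0.925 | 0.619 | 0.651 |

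The adjusted figures are slightly favourable, since the closed form ignores the cost of estimating the baseline slope. At rho 0.5 a simulation of 20,000 trials gave 0.794 rather than 0.815.

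If 0.9 is instead the SD of a single measurement, power is 0.481 v 0.791 at rho 0.3 and 0.831 v 0.912 at rho 0.7. The two readings coincide at rho 0.5. For a constant effect of 1.0 at rho 0.5, power is 0.924 v 0.990.

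**Baseline as a fourth level, group-by-time test.** For effects 0, 1/3, 2/3, 1, the squared deviations from their mean sum to 0.556. With σ²(1 − rho) = 0.405, the noncentrality is 0.556/(0.405 × 0.15) = 9.15, and F(3, 84) gives power 0.697 at every rho. The adjusted three-visit mean has 0.815 at rho 0.5, 0.727 at 0.7 and 0.688 at 0.8, so for a linear effect the advantage has gone by about 0.8. For a constant effect the interaction has 0.833, against 0.990 adjusted at rho 0.5 and 0.970 at 0.7.

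**Agreement at week 12.** The SD of a chance baseline difference at rho 0.5 is 0.9 × √0.15 = 0.35. A difference of that size moves the change-score estimate by (1 − 0.5) × 0.35 = 0.17. In 5,000 simulated trials per setting with a true difference of 1.0, unadjusted change and analysis of covariance at week 12 compared as follows:

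| rho | power, change | power, covariance | opposite sides of 0.05 | SD of gap in estimates |
|---|---|---|---|---|
| 0.5 | 0.79 | 0.88 | 13% | 0.18 |
| 0.7 | 0.79 | 0.84 | 10% | 0.15 |
| 0.9 | 0.79 | 0.80 | 6% | 0.10 |

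With no true effect, both methods rejected in about 5% of trials and disagreed in 3% to 4%.

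**The case against.** The strongest reply is that the point rests on a label. Neither analysis has its covariates listed, the article condenses a fuller protocol, and nothing expressly keeps baseline out of the repeated-measures model. This stands as a limit: a reader should not infer that the trial has ruled out baseline adjustment. It does not dispose of the point. The article names a method, and as named that method has no covariate, directly after one that does.

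Second, no decision hangs on this analysis. The primary endpoint is week-12 change, and the article's 0.05 threshold is attached to the primary outcome only. This is correct and limits the weight of the point.

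Third, the gap of 62% against 82% belongs to one way of running the analysis at one assumed rho. On the four-level reading the comparison at rho 0.5 is 70% against 82%. At rho 0.8 the interaction test is marginally ahead for a linear effect (69.7% v 68.8%). This also stands.

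Fourth, the SD and the difference are those of capillary density. Whether it is measured at weeks 4 and 8 is not in the text shown: the Assessments section lists visits, and the schedule of procedures is in a figure that is not reproduced. The power figures are illustrative to that extent.

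Fifth, baseline adjustment cannot apply to mRSS, which the Inclusion criteria and the Study outcome rationale put at 0 for everyone at entry. The replacement sentence has to allow for this.

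Last, a treatment effect averaged over three visits can differ from a week-12 effect under any method. Only the week-12 contrast can be brought into line.

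**Conclusion.** The point holds as a modest one. The named method for weeks 4, 8 and 12 does not use a baseline value that the trial collects, and a better method costs almost nothing.

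On the change-score reading, with 0.9 as the SD of change, the gain in power for a linear effect is about 29 points at rho 0.3, 20 at 0.5, 11 at 0.7 and 3 at 0.9. On the four-level reading the gain for a linear effect is smaller and disappears at about rho 0.8. All of this rests on 20 v 10, compound symmetry, a correlation that the documents do not give, and the capillary density SD.

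A reader might infer that the treatment effect would be biased or that the trial's main result is at risk. The documents do not support either. Type I error is near 0.05 with or without adjustment, chance imbalance averages out over repeated trials, and the primary comparison is the separate week-12 analysis of covariance. Nor is the stated method always the less powerful one, as the four-level reading shows. What is lost is precision in a supporting analysis and agreement between two week-12 estimates in the same report.

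**What to change.** Replace the sentence on weeks 4, 8 and 12 with:

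> Changes from baseline at weeks 4, 8 and 12 in the continuous outcomes will be analysed with a repeated-measures linear model with unstructured within-patient covariance and with treatment, visit, treatment-by-visit, baseline value and baseline-by-visit as fixed effects; baseline is a covariate and not a response level. For outcomes with a constant baseline (mRSS, 0 by eligibility) the baseline terms are omitted. The treatment difference is reported at each visit, and the week-12 contrast uses the same baseline covariate as the week-12 analysis of covariance.

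The last clause also makes explicit that the week-12 analysis of covariance adjusts for baseline, which the article leaves to be inferred.

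The cost is one passage of text and up to three residual degrees of freedom for the baseline terms. No patients, visits or measurements are added, and the sample size of 30 does not change.
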